### Strategies to improve adherence to interventions {11c}

Video-game based swallowing rehabilitation programs are safe with multiple game components, so high compliance with the program is expected. Adherence is based on the actual completion of the patient's swallowing function training. The actual completion of the dysphagia training by patients, including the number of training sessions completed and the duration of the training, is objectively recorded by the researcher. In addition to this, participants will be asked to complete a daily training diary in which they record the training activities they perform and record the duration, intensity, and symptoms of discomfort.

### Relevant concomitant care permitted or prohibited during the trial {11d}

Patients are allowed to receive other necessary basic care, such as daily feeding education, position training, breathing control, and improving cough technique, and medications. Each group will be given the same duration and intensity of basic usual care, using standardized operating procedures, in order to reduce the effect of usual care on the effectiveness of the intervention. The progress and status of treatment in both groups will be monitored weekly to ensure that usual care is performed consistently.

### Provisions for post-trial care {30}

There is no anticipated harm and compensation for trial participation. Neither the measurements nor the game manipulation produces any significant harmful side effects, as the game does not have graphic depictions of violence, and any of our measurements are not invasive.

### Outcomes {12}

All assessments were completed by an experienced occupational therapist who was blind to the participants' group assignments. Assessments were conducted before the start of the intervention (pre-training), after 4 weeks of treatment (post-training), and at the 1-month follow-up (follow-up).

The primary outcome of this study was swallowing function, assessed using the Toronto Bedside Swallowing Screening Test (TOR-BSST) and the Functional Oral Intake Scale (FOIS). The Toronto Bedside Swallowing Screening Test (TOR‐BSST) is the best performing water swallow screening tool [21] with a sensitivity of 91.3%, a negative predictive value of 93.3% in the acute phase and 89.5% in the recovery phase [22]. TOR-BSST has shown to be more convenient and cheaper in bedside screening compared to the gold standard method of simultaneous videofluoroscopy (VFSS), which is an invasive assessment. Due to the limitations of the experimental site, we chose TOR-BSST as the assessment tool for dysphagia. FOIS consists of a 7-point scale, with level 1 indicating completely impaired oral intake and level 7 indicating complete oral intake regardless of food concentration or type [23].

Secondary outcomes in this study were quality of life, nutritional status, satisfaction and adherence. The swallowing quality of life (SWAL-QOL) questionnaire consists of 10 subscales and a symptom scale (14 items) to assess the severity of dysphagia symptoms. Scores range from 0 to 100, with lower scores indicating greater impairment of quality of life from dysphagia [24]. Body mass index (BMI) and Mini Nutritional Assessment Short Form (MNA-SF) were used to assess the nutritional status of the dysphagia patients. BMI is one of the most commonly used nutritional assessments among adults [25]. MNA-SF is commonly used to screen patients for malnutrition or risk of malnutrition with high sensitivity and specificity [26]. MNA-SF in combination with BMI showed higher accuracy [27]. The satisfaction questionnaire was designed based on the literatures. There are 15 items, involving 3 dimensions: training mode content setting, training mode format setting, and self-subjective feeling, and scored on a 5-point Likert scale. The higher the score, the more satisfied the patients were with the video-game training. Adherence was considered good if the patient could complete more than 80% of the training sessions of the corresponding training program; average if the patient could complete 50% to 80% of the training sessions; and poor if the patient could complete less than 50% of the training sessions. Patients are considered to have completed their training when they have completed more than 12 training sessions [28].

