### Eligibility criteria {10}

The inclusion criteria were: (1) diagnosis of dysphagia according to the Toronto Bedside Swallowing Screening Test (TOR‐BSST); (2) age between 18 and 80 years; (3) no significant cognitive impairment, able to execute instructions correctly, and with Mini-Mental State Examination (MMSE) score ≥ 24; (4) be able to use a computer screen with or without the assistance of others; (5) be able to understand and follow instructions; (6) life expectancy estimated by healthcare providers to be ≥ 12 months; and (7) informed consent to the study can be given by signing an informed consent form.

The exclusion criteria were: (1) dysphagia caused by structural lesions (eg, radiotherapy, previous extensive surgery of the head and neck region such as laryngectomy and cordectomy); (2) combined with serious heart, lung, liver, kidney diseases, and hematological disorders; (3) limb deficiency or paralysis, blindness in both eyes, severe visual impairments; (4) motion sickness or vestibular dysfunction; (5) history of epilepsy, malignancy or other neurological diseases; or (6) pregnancy or breastfeeding. Some of the exclusion criteria depended on the video-game device or were precautions designed to not harm participants after using video-game technology. Because of the need to use video games, there is concern that people over the age of 80 will not be able to use computers or view electronic screens, thus limiting participants under the age of 80.

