## Statistical methods

### Statistical methods for primary and secondary outcomes {20a}

An intention-to-treat analysis will be performed, and the last available measurement will be used when data were lost due to dropout. Statistical analysis will be performed using SPSS 29.0. Statistical significance of all outcome variables will be established at *P* < 0.05.

All continuous data will be tested for normality, and nonparametric tests will be used for non-normally distributed data. Data conforming to normal distribution will be expressed as mean ± standard deviation (SD), and data with non-normal distribution will be expressed as median (interquartile range).

Comparisons of continuous data of two groups at the same time will be analyzed using independent samples t tests or rank sum tests, and comparisons of two groups of rates will be performed using chi-square test or Fisher exact test [31].

Comparison of continuous data trends over time between different groups at different times, if data normality is present, we will perform a series of repeated measures analysis of variance (ANOVA) for each outcome measure to assess differences between time (4 weeks and 1 month post) and between study groups, as well as interactions between time and study groups. For these analyses, the assumptions of sphericity and homogeneity of variances are tested using Mauchly and Levene tests [32]. If the assumption of sphericity is violated, the Huynh–Feldt correction is applied [32].

If the normality assumption is not met, the linear mixed model will be used for analysis, the comparative analysis at each time was performed using the nonparametric statistical Mann–Whitney U test and its own control two-way comparison using the nonparametric statistical Kruskal–Wallis rank sum test [33].

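### Two unranked primary measures, read at two visits and each tested at P < 0.05 with no rule for success, leave either the 5% error rate or the 90% power unsecured; only FOIS was used to size the trial

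*Protocol article*

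**What the plan says.** Outcomes {12} defines the primary outcome through two instruments: "The primary outcome of this study was swallowing function, assessed using the Toronto Bedside Swallowing Screening Test" (TOR-BSST) "and the Functional Oral Intake Scale (FOIS"). Neither is placed above the other. After baseline, both are assessed "after 4 weeks of treatment (post-training), and at the 1-month follow-up (follow-up"), and neither visit is called primary.

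Statistical methods {20a} sets one threshold for everything: "Statistical significance of all outcome variables will be established at *P* < 0.05". It plans group comparisons visit by visit ("Comparisons of continuous data of two groups at the same time will be analyzed using independent samples t tests or rank sum tests") and chi-square or Fisher tests for rates. For continuous data over time it adds a repeated measures ANOVA with group, time and interaction effects. It does not say which of these is the deciding test. Additional analyses {20b} relies on a primary analysis without identifying it.

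Sample size {14} uses FOIS only: means 5.40 and 4.40, SDs 1.70 and 0.80, significance level 0.05, power 90%, 31 per group, raised to 78 in total for 20% dropout. It gives neither a visit nor the sidedness of the test. No expected rate, effect or power for TOR-BSST appears.

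TOR-BSST is also the entry test: Eligibility criteria {10} requires "diagnosis of dysphagia according to the Toronto Bedside Swallowing Screening Test".

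**The concern.** Objectives {7} makes one superiority claim, that the video game improves swallowing function more than conventional training. Up to four group comparisons (two measures at two visits) could each be offered as proof of it. The protocol has no hierarchy, no division of the significance level and no requirement that both measures succeed.

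That leaves two readings, and each damages a stated property of the design. If any significant result may be called success, the 5% level does not apply to the trial's conclusion. If both measures must be significant, the error rate is protected, but the 90% power was worked out for FOIS alone and cannot be claimed for the joint result. A choice between these readings made after the data are seen would not be credible.

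**Working it through.** **Step 1. Reproduce the plan's sample size.** The inputs are from Sample size {14}.
- SD = √((1.70² + 0.80²)/2) = √1.765 = 1.3285.
- d = (5.40 − 4.40)/1.3285 = 0.753.
- One-sided 0.05, noncentral t: 31 per group gives 90.1% power, which matches the stated 31.
- Two-sided 0.05: 90% power needs 39 per group (38 by the normal approximation). With 31 per group the power is 83.0%; with 39 it is 90.7%.
- Dropout: 62/(1 − 0.20) = 77.5, rounded up to 78, which matches.

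So the stated figures reproduce, but the 31 per group does so only with a one-sided test.

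**Step 2. Error if any result can win.** The inputs are 0.05 per test ({20a}), two measures and two post-baseline visits ({12}). Under independence:
- two tests: 1 − 0.95² = 9.75%;
- four tests: 1 − 0.95⁴ = 18.5%.

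The tests will be correlated, and the protocol gives no correlation. Assumed common correlations were therefore used, with 1 million simulated sets of normal statistics, each tested two-sided at 0.05:

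| Correlation | Two measures, one visit | Two measures, two visits |
|---|---|---|
| 0 (exact) | 9.75% | 18.5% |
| 0.3 | 9.6% | 17.4% |
| 0.5 | 9.0% | 15.6% |
| 0.7 | 8.3% | 13.0% |
| 0.9 | 7.1% | 9.4% |

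With different assumed correlations between visits (0.7 to 0.9) and between measures (0.3 to 0.5), the four-test rate is about 13–16% (12.7% to 15.6%).

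**Step 3. Power if both must win.** Joint power cannot exceed the lower of the two separate powers. The FOIS power is stated as 90%; the TOR-BSST power is unknown. As an illustration only, if TOR-BSST also had 90% and the two were independent, joint power would be 0.90 × 0.90 = 81%.

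**Step 4. Cost of splitting the significance level instead.** FOIS power, two-sided, same d:

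| Level per test | 31 per group | 39 per group |
|---|---|---|
| 0.05 | 83.0% | 90.7% |
| 0.025 (two tests) | 74.5% | 84.8% |
| 0.0125 (four tests) | 65.1% | 77.6% |

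By the normal approximation, 90% power would need 44 per group at 0.025 and 51 at 0.0125. A single primary test is therefore much the cheaper repair.

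**The case against.** The strongest reply is that this is a condensed article, that an analysis plan may exist, and that the inflated rates rest on a rule the protocol never states. The first part does not remove the point. The article itself selects two primary measures and fixes an unadjusted 0.05 for every outcome; the criticism is of what it states. The second part stands as a limit on the numbers:

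- A reader might take 19% as the trial's actual error rate. The documents do not support that. It needs four independent tests, which is implausible for the same patients measured twice on related scales. Carrying the last value forward, as {20a} plans, would raise the correlation between visits further.
- If one repeated-measures test per measure decided, the rate would be about 7–10%.
- The rates count errors in either direction. In favour of the video game only, four two-sided tests give about 5–10% (correlation 0.9 to 0), against 2.5% for a single two-sided test.
- Fisher's exact test on a pass/fail TOR-BSST is conservative: about 3% true size with 39 per group at assumed pass rates of 20–50%. This lowers the totals somewhat.

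A reader might also infer that ANOVA is planned for a positive/negative TOR-BSST result. Section {20a} does not say so: it introduces the ANOVA for continuous data and provides chi-square or Fisher tests for rates. Nor is it a defect that all participants are positive on TOR-BSST at entry; the proportions still positive can be compared validly.

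Finally, the Discussion presents the trial partly as preparation for a larger one. That lessens the consequences, but Objectives {7} still states a superiority hypothesis.

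**Conclusion.** The point holds. The protocol names two unranked primary measures at two visits, tests all at P < 0.05, gives no rule for success and sizes the trial on FOIS alone. If any result may win, the chance of at least one false positive is about 8–10% for two measures at one visit and about 13–19% for two measures at two visits. Both ranges depend on assumed correlations of 0.7 to 0 and on the any-win reading. If both measures must win, there is no inflation, but the 90% power is not shown.

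That FOIS itself has 90% power is true at 31 completers per group only for a one-sided 0.05 test, a sidedness the protocol does not state.

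**What to change.** Before recruitment starts:

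1. Name FOIS at one stated visit, with one between-group test, as the single primary analysis. Week 4, the end of treatment, is the natural visit, but this is a suggestion; Sample size {14} names none.
2. Make TOR-BSST secondary, as the proportion still positive, compared by the chi-square or Fisher test already planned. Make FOIS at the other visit secondary as well.
3. State whether the primary test is one- or two-sided and restate the power to match. At two-sided 0.05 it is about 83% with 31 completers per group and about 91% with 39 per group, i.e. with no dropout. The sponsor should either accept the lower figure or enlarge the trial: 39 completers per group with 20% dropout means 78/0.80 = 97.5, or 98 in total.
4. Check the registry entry, which was not seen here, and align it if it differs.

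Items 1, 2 and 4 cost only wording, plus the loss of primary status for TOR-BSST. Trial status describes the study as not yet recruiting, and the amendment section already provides for registry updates. Item 3 costs either a lower stated power or about 20 more participants (98 − 78).

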### Sample size {14}

The sample size was calculated from a previous study conducted by Park et al. [29] in dysphagia patients, which measured patient swallowing function on the Functional Oral Intake Scale (FOIS), with mean of 5.40 and 4.40, SDs of 1.70 and 0.80 for the intervention and control groups, respectively. For a significant level of 0.05 and power of 90%, 31 participants were estimated in each group (62 participants). Finally, to avoid loss of power due to potential dropout, the sample size was increased by 20% for each group, resulting in a total number of participants of *N* = 78. The sample size was estimated using G-Power 3.1 [30].

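### The primary outcome is two measures at two post-baseline visits, each tested at an unadjusted 0.05, and the protocol names no deciding measure, visit, test or success rule

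*Protocol article*

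**What the plan says.** The Objectives section of the protocol article gives one directional hypothesis: swallowing function improves more with the video game than with conventional training.

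The Outcomes section defines the primary outcome: "The primary outcome of this study was swallowing function, assessed using the Toronto Bedside Swallowing Screening Test" (TOR-BSST), with the FOIS named beside it as a second instrument. It schedules assessments before training, after 4 weeks of treatment and at a 1-month follow-up, which makes two post-baseline visits.

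The section on statistical methods for primary and secondary outcomes sets one threshold: "Statistical significance of all outcome variables will be established at *P* < 0.05". It then plans two layers of testing:

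- Per visit: "Comparisons of continuous data of two groups at the same time will be analyzed using independent samples t tests or rank sum tests", with chi-square or Fisher tests for rates.
- Across visits: a repeated-measures ANOVA for each outcome measure, with time, group and interaction terms. A linear mixed model plus rank tests replaces it if normality fails.

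The section on additional analyses relies on a primary analysis being sufficient, but no section says which analysis that is.

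The Sample size section rests on an earlier study "which measured patient swallowing function on the Functional Oral Intake Scale (FOIS"). It names no visit and does not call FOIS the deciding measure.

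**The concern.** A single hypothesis is to be judged on two measures, two visits and more than one type of test, each at 0.05. As written, a report could claim that the game improves swallowing function on whichever comparison reaches significance. The protocol does not say what follows if FOIS and TOR-BSST disagree, or if week 4 and follow-up disagree.

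The point does not rest on detail that an analysis plan might supply. The protocol itself makes two measures primary and itself fixes an unadjusted 0.05 for each. A later plan that named one of them would be changing the protocol's definition of the primary outcome.

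The point concerns the primary claim only. It does not concern the secondary outcomes or how suitable TOR-BSST is as an instrument.

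**Working it through.** **Inputs from the protocol.** Two primary measures and two post-baseline visits (Outcomes). P < 0.05 for each outcome variable (Statistical methods). FOIS means 5.40 and 4.40, SDs 1.70 and 0.80, alpha 0.05, power 90%, 31 per group, 20% dropout, N = 78 (Sample size).

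**Assumed, because the protocol does not give them.** The correlation between visits, the correlation between measures, how TOR-BSST is scored, and the success rule. The Discussion says that the trial will itself help to estimate correlations between measurement times.

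**1. The protocol's own figure.**
- Pooled SD = √[(1.70² + 0.80²)/2] = 1.3285, and d = 1.00/1.3285 = 0.753.
- One-sided 0.05 with 90% power: 30.93, so 31 per group. This matches.
- Two-sided 0.05 with 90% power: 38.08, so 39 per group. This does not match. At two-sided 0.05, 31 per group gives 83.0% power and 39 per group gives 90.7%.
- Dropout: 31/(1 − 0.20) = 38.75, so 39 per group and N = 78. This matches.

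The stated 90% is therefore a FOIS-only figure and reproduces only for a one-sided test. The protocol does not state sidedness.

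**2. Any one of four comparisons counts, each two-sided at 0.05.** If the tests were independent, 1 − 0.95⁴ = 18.5%. With correlated test statistics (1,000,000 simulated null draws per setting):

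| Visit correlation | Measure correlation | Chance of at least one P < 0.05 |
|---|---|---|
| 0.3 | 0.3 | 17.7% |
| 0.5 | 0.5 | 16.1% |
| 0.7 | 0.5 | 14.9% |
| 0.8 | 0.5 | 13.9% |
| 0.8 | 0.7 | 12.8% |
| 0.9 | 0.7 | 11.6% |

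A second simulation used 39 per arm, a 7-level FOIS compared by t test, and TOR-BSST read as pass/fail with an assumed 40% passing. It gave 15.3–18.8% with chi-square and 12.2–15.4% with Fisher's test, which is conservative.

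**3. One overall test per measure, either counts.** If independent, 1 − 0.95² = 9.75%. For measure correlations of 0.3 to 0.7, 9.5% down to 8.3%.

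**4. Any of four, counting only results that favour the game.** The nominal rate is 2.5%. If independent, 1 − 0.975⁴ = 9.6%. With correlations 0.5/0.5 (visit/measure) it is 8.1%, with 0.7/0.5 it is 7.4%, and with 0.9/0.7 it is 5.8%.

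**5. Both measures must succeed.** The type I error is then at most 5%. Joint power cannot exceed the FOIS power and will generally be lower. By how much cannot be worked out, because the protocol gives no expected TOR-BSST effect.

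**The case against.** Several objections have force.

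- **The size is conditional.** No section says that any one of four results suffices. A reader might infer that the plan carries a fixed error rate of about 15–18%. The documents do not support that: the figure needs an any-of-four rule and moderate correlations, neither of which they state. Higher visit correlations or Fisher's test bring it down to about 12%.
- **Four separate tests is not the only reading.** The repeated-measures ANOVA could be meant as the one deciding test for each measure. That leaves two tests and about 8–10%. Since the hypothesis is directional, false claims of benefit run at about half the two-sided any-of-four rate.
- **FOIS may be the implied lead.** The trial is sized on it. A reader might infer that every reading of the plan breaks either the 5% level or the 90% power, but an FOIS-led reading would escape that dilemma. The hint is not binding, however. The Sample size section names no visit, and the Outcomes section lists TOR-BSST first and presents it as the chosen assessment tool for dysphagia.
- **The joint power cannot be quantified.** A reader might want a TOR-BSST power for some assumed pair of pass rates. Any such pair would have no basis in the protocol, so the point stops at saying that 90% was computed for FOIS alone.
- **The trial is modest in scope.** It is a single-centre trial of 78 patients, and the Discussion presents it partly as preparation for a larger one. That tempers the severity.

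None of this supplies a deciding measure, visit, test or rule. Every any-success reading that was tried stays above its nominal level.

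**Conclusion.** The structural gap is plain in the text: two primary measures, two post-baseline visits, two layers of tests, a flat 0.05, and nothing that says what decides.

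The size depends on a rule that the protocol leaves open:

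- Any of four comparisons, two-sided: about 12–18.5%. The upper end is independence; the lower end is a visit correlation of 0.9 with a measure correlation of 0.7.
- One overall test per measure, either counts: about 8–10%.
- Any of four, only results favouring the game: about 6–10% against 2.5%.
- Both measures required: the 5% level holds, but the stated 90% power does not describe the joint claim.

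Confidence is high in the gap and moderate in the figures, which rest on assumed correlations and, in the per-arm simulation, on a pass/fail reading of TOR-BSST. Severity: should-fix.

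**What to change.** In the Outcomes and Statistical methods sections, name one primary endpoint and one primary test at two-sided 0.05. One option is the between-group comparison of FOIS at week 4, which is the measure the trial is sized on, taken at the end of treatment. The test must be named in advance as well. Otherwise the t test, rank-sum test, ANOVA terms and mixed model would all remain available for that endpoint, and the 5% would not be secured.

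Make FOIS at follow-up and TOR-BSST at both visits secondary. Either test them in a fixed order, each only if the one before is significant, or report them descriptively.

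If the investigators prefer to keep both measures primary, they should name one visit and one test per measure, and then do one of two things:

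- state that both must succeed, and restate the power for that joint claim; or
- split alpha between the measures and restate the power. At two-sided 0.025, FOIS alone needs 45.09, so 46 per group for 90% power, before dropout.

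**Cost.** With a single primary endpoint the change is wording in the protocol, the registry entry and any analysis plan, with no extra patients or visits. The Trial status section places the trial before recruitment, so the change can be made before any data are seen. Two consequences should be accepted openly. A benefit seen only on TOR-BSST or only at follow-up could not be claimed as the primary result. And stating a two-sided test means restating the power: 83.0% with 31 analysed per group, or 90.7% if all 39 per group are analysed.

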**Methods:**

A randomized controlled trial with 4 weeks of intervention and 4 weeks of follow-up will be conducted in a rehabilitation center in Beijing, China. We will enroll 78 patients aged 18–80 years with dysphagia. Participants will be randomly assigned to the experimental group (video-game based swallowing function training) and the control group (conventional swallowing function training). All participants will receive 30 min of training per day, 5 times per week, for a total of 4 weeks. The primary outcome is swallowing function. Secondary outcomes include patients' quality of life, training compliance, and training satisfaction. Outcomes are assessed at baseline (pre-treatment), 4 weeks of treatment (post-treatment), and 8 weeks (follow-up), and the assessor is not aware of the participants’ grouping.

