## Interventions

### Explanation for the choice of comparators {6b}

We wish to observe the effect of video games on the rehabilitation of swallowing function. Therefore, the control group use the same components of the rehabilitation program without the video game effect. Both groups have the same duration of intervention.

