### Procedure for unblinding if needed {17b}

N/A: Only outcome evaluators in this study will be blinded, so unblinding will not occur.

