## Data collection and management

### Plans for assessment and collection of outcomes {18a}

Each participant will be assessed individually three times, pre-intervention, post-intervention and follow-up. The assessments will focus on swallowing function, quality of life, nutritional level and satisfaction with video games. Data will be collected by the investigators on site using case report form (CRF). All data obtained during the study will be anonymized and stored in folders in a protected research server at the Hong Kong Polytechnic University. Only the research team is allowed to access the folder.

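### The satisfaction score is defined as satisfaction with the video game, so it gives no valid comparison with controls, and if the blinded assessor takes the answers they can reveal the arm

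*Protocol article*

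**What the plan says.** **What is measured.** Outcomes {12} lists satisfaction as a secondary outcome, with no restriction to one arm. It is a 15-item, 5-point Likert questionnaire built by the team, with three dimensions: "training mode content setting, training mode format setting, and self-subjective feeling". The score is then read as follows: "The higher the score, the more satisfied the patients were with the video-game training". Plans for assessment and collection of outcomes {18a} gives the same meaning: "The assessments will focus on swallowing function, quality of life, nutritional level and satisfaction with video games". The abstract (Methods) uses a neutral label instead, listing "training compliance, and training satisfaction" among the secondary outcomes.

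**Who could answer.** Under Explanation for the choice of comparators {6b}, "the control group use the same components of the rehabilitation program without the video game effect". The control training in Intervention description {11a} likewise contains no game.

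**When.** Section {18a} says: "Each participant will be assessed individually three times, pre-intervention, post-intervention and follow-up". The abstract gives the same three time points for outcomes in general. Table 1, the schedule by measure, is not shown in the text available.

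**By whom.** Outcomes {12} states: "All assessments were completed by an experienced occupational therapist who was blind" to group. The same section names TOR-BSST and FOIS as the primary outcome. Section {18a} has investigators on site collecting data, the Discussion refers to questionnaire investigators, and Strategies to improve adherence {11c} has the researcher recording adherence.

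**Blinding.** Section {17b} states: "Only outcome evaluators in this study will be blinded, so unblinding will not occur".

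**The concern.** A secondary outcome of a parallel-group trial needs the same meaning in both arms. A score that expresses liking for the game has that meaning in only one arm. Whatever number a control patient produces, the difference between arms cannot be read as a difference in satisfaction with training.

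The second issue is blinding. Participants and therapists know the allocation, so only the assessor's ignorance of it protects the assessor-rated swallowing measures. A questionnaire about the game, taken by that assessor at the visits where swallowing is rated, is a foreseeable route to disclosure. Section {17b} rules unblinding out without considering it.

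**Working it through.** No stated figure depends on this point, so there is nothing to recompute. The check is a comparison of the sections.

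1. **Is the game-specific meaning a single slip?** No. It appears in the scoring sentence of {12} and again in {18a}. In {12}, adherence is scored against whichever programme the patient was assigned, so neutral wording was available and was not used for satisfaction.

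2. **Does the rest of the article agree with that meaning?** No. The abstract's label and the three dimension names refer to training, or to the mode of training, and would fit either arm. The article therefore carries two definitions.

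3. **Is a comparison between arms implied?** Yes, though only in general terms. Satisfaction is an unrestricted secondary outcome, and Statistical methods {20a} plans repeated-measures ANOVA for each outcome measure, with time, group and interaction effects. Under the definition in {12} and {18a}, the group and interaction terms have no valid control-arm data behind them. A pre-training value would have no meaning in either arm.

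4. **Is it collected before training?** Read literally, {18a} and the abstract place it at all three visits. But adherence is also a secondary outcome and cannot exist at baseline, so the three-visit statement cannot apply literally to every outcome. Table 1 might settle this and is not shown. Baseline collection is therefore possible but not established.

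5. **Does the blinded therapist administer it?** Read literally, {12} says so, and the abstract says the assessor does not know the grouping directly after naming the outcomes. Against this, {11c} shows that the therapist does not handle every secondary outcome, and {18a} and the Discussion mention investigators without stating whether they are blinded. The article is inconsistent here. It neither names an unblinded administrator for this questionnaire nor exempts it from the blanket statement in {12}.

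6. **How would blinding be weakened?** An identical form put to every patient discloses nothing by being asked. The answers can disclose the arm, as can giving the form to the game arm only. Either matters only if the blinded therapist sees or hears it, and for ratings made at the same visit only if it comes before the swallowing tests. The article does not state the order of tests within a visit.

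**The case against.** The strongest reply is that this is loose drafting. The 15 items are not shown, the dimensions are neutral and the abstract speaks of satisfaction with training, so controls may well be asked about their own programme. The game phrases would then be shorthand. Satisfaction might also be meant as a description of the game arm only: the hypothesis in Objectives {7} concerns swallowing function, and the closing paragraph of the Discussion names swallowing function, quality of life and adherence but not satisfaction. Item wording, visit order and handling of forms are commonly left to the full protocol.

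Much of this stands as a limit on the point. A reader might infer that no control could answer the questionnaire, that asking it unmasks every patient, and that the blinded therapist certainly collects it at all three visits. The documents do not support those readings: the items and Table 1 are not shown, an identical form does not identify the arm, and the administrator is stated inconsistently.

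The core remains. The article does more than omit detail: it states twice what the score means, and that meaning does not fit an unrestricted two-arm outcome. If a game-arm description was intended, the article does not say so. The blanket assignment of assessments to the blinded therapist is also written, without exception.

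**Conclusion.** The point holds in limited form. As defined in {12} and {18a}, the satisfaction score supports no valid comparison between arms and has no meaning before training. The abstract and the dimension names point to a different, usable definition, so the sections must be reconciled. The threat to assessor blinding is conditional: it arises if the blinded therapist takes the answers, and ratings at that same visit are exposed only if the swallowing tests come afterwards.

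The size of that threat is unknown. One could assume a rating bias on FOIS and compute the resulting type I error, but the bias would be invented and the result would apply equally to any other route of unblinding. Patients who know their arm could also disclose it in ordinary conversation, so the extra risk from this questionnaire cannot be isolated. The conclusion rests on the wording alone and would soften if the items prove neutral, or if Table 1 or the full protocol restricts timing and administration. The change is worth making before recruitment because it removes an avoidable risk at almost no cost.

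**What to change.** - In {12} and {18a}, define the outcome as satisfaction with the allocated training, with identical neutral items and scoring in both arms. Alternatively, state that it is a descriptive measure in the game arm only and will not be compared between arms.
- Collect it only after training: at week 4, and at week 8 if wanted.
- Have it self-completed and returned in a sealed form, or handled by existing staff other than the blinded assessor, after the swallowing tests at that visit. If it is game-arm only, the blinded assessor should not know who receives it.
- Exempt it from the blanket statement on assessments in {12}, and bring the abstract, {12}, {18a} and the Discussion into line on what is measured and who administers it.

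The cost is rewording a questionnaire the team designed itself and fixing the order of tasks within a visit, with no extra patients or staff. The downside is that any game-specific items become descriptive, for the game arm only.
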